## 7. Discussion

The PACO study will examine the effects of a school-based cycling intervention on adolescent´s cycling to school, ACS, and PA. Several possible mediators influencing the effects of this intervention will be examined based on SDT and SEM frameworks. In addition, an evaluation of its potential for public health impact using the RE-AIM framework will be conducted.

The main purpose of the PACO study has clear social implications, since the school-based intervention has been designed and piloted prioritizing feasibility and usefulness for implementation during PE sessions in secondary schools. The PACO study has been recreated to fit the PE and school context, to ensure a more likely successful implementation [81]. The difficulty of implementing quasi-experimental and randomized controlled trial designs in the school setting due to high variability within schools in relation to factors such as teachers, students, and organizational issues is well known [46]. Previous reviews on school-based interventions to promote ACS outlined the low quality of intervention designs used [22,25], identifying only few RCTs and a lack of theoretical frameworks. In this regard, the PACO study has combined two approaches to be relevant to both research and practice. The randomized controlled trial design used in this study is one of the major strengths. In addition, the study incorporates several theoretical frameworks. The study also provides user-friendly material for promoting cycling in schools that may contribute to the maintenance and sustainability of the intervention in the medium and long terms.

In the search for balance, several pragmatic adaptations will be made to conduct the research in “real-world” scenarios (such as school) where decisions need to be made on how to best conduct the study with the limited amount of time and resources that researchers may have [82]. In the PACO study, these adaptations pertain to the study design, implementation, and evaluation. Firstly, the school teachers will be able to choose the participating class groups, within the same grade. The pilot study and several consultations with school teachers showed that teachers want to choose the participating class and this will increase their involvement in the intervention. Secondly, all high schools in the three participating cities will be included in the random selection processes and then, the chosen schools will be invited to participate. Time limitations do not allow to visit each school for this purpose, and emails to schools have been previously sent (in previous studies of the research group) and they have not been answered because of high workload. Consequently, we will include all the schools in the random process to guarantee that everyone has the same likelihood to be selected. Thirdly, the intervention includes 4 sessions during a 1-month period. Research staff will offer the option to teachers of spreading the 2 h lesson of the 2nd and 4th session in two 1 h sessions using the normal PE schedule. In Spain, the national educational system in secondary schools mandates 2 h per week of PE. Fourthly, regarding the organization of the academic year in 3 trimesters, the study will be implemented in full trimesters to avoid holiday times, including the assessments. Finally, the cycling skills will be assessed by the teacher using a checklist twice during the intervention, simulating real evaluation conditions. However, safety (e.g., to avoid risky activities where children perform skills that they have not learned yet) and time limitations (e.g., lack of more PE sessions to enlarge the intervention), will prevent the cycling skills assessment being carried out at baseline and follow-up, respectively. To summarize, doing research in schools is important to prevent unhealthy behaviours and related beliefs common in our society. Achieving a balance between the scientific requirements of randomized designs and the constraints imposed by real world circumstances is necessary to improve the quality of research conducted in educational settings [83]. It is also consistent with recent calls to achieve a balance between the established evidence-based pathway and a practice-based evidence pathway, and for a more nuanced approach to appraising the utility of diverse types of evidence [84].

The intended outcomes in the PACO study are to increase the number of participants using cycling or other active modes of commuting to school and PA levels. However, there is evidence about the difficulty of changing behaviours though school-based interventions. For example, the rigorously developed school-based Go Active intervention was no more effective than standard school practice at increasing adolescent PA [83]. Therefore, mediators must be measured to identify the pathways for achieving future behaviour changes. Actually, previous reviews of school-based interventions to promote ACS concluded about the lack of inclusion of mediators in the statistical analyses [22,25]. In the current study, an in-depth analysis of mediators is proposed based on SDT and SEM. The effects of the intervention in the mediators, as well as possible effects of the mediators on the main outcomes, will be analysed. The presence of an appropriate control group is crucial to assess the effects of the intervention. The findings from the PACO study will extend current knowledge about the effectiveness of a cycling school-based interventions to increase active modes of commuting and physical activity levels among secondary school students.

Strengths of the PACO study include the study design (i.e., randomised controlled trial), the inclusion of proposed mediators of the effects of the intervention, the use of theoretical frameworks (i.e., SDT and SEM) and the use of internal and external validity indicators of study design and assessment of implementation processes guided by the RE-AIM framework. The limitations include the low sample size, the short duration of the intervention, the lack of family involvement in the intervention, uncertainties surrounding the engagement and cooperation of school teachers, and the lack of assessment of cycling skills and the maturity at baseline and post-intervention.

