## 2. Methods

### 2.1. Study Design

The PACO study is a randomized controlled trial setting in public high schools from three Spanish cities (Granada, Jaén, and Valencia), where the schools are the units of randomization, and individuals within the schools are the units of analysis (the participants). The intervention focuses on promoting cycling to school and will be implemented in adolescents during 1 month within the physical education (PE) curriculum classes. Six high schools (i.e., an intervention and a control school in each of the 3 involved cities) will be randomly selected to participate. All study participants will be assessed before and after the intervention period using assessment procedures described below.

The PACO study has been approved by the Review Committee for Research Involving Human Subjects at the University of Granada (Reference: 162/CEIH/2016) and registered with a ClinicalTrials.gov ID: NCT03937336. In addition, the present study protocol has been written in accordance with the Standard Protocol Items: Recommendations for Interventional Trials (SPIRIT) statement (see supplementary file 1).

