### 2.2. Study Population

A total of 360 adolescents aged 14–15 years (3rd grade of secondary education; hereinafter called 3rd grade) from 6 high schools located in 3 Spanish cities will be recruited (see Figure 2). The randomization process is presented in the Figure 2. Within each city, 2 high schools, randomly selected and allocated to intervention or control treatment, will participate in the study. Within each secondary school, two class groups of approximately 30 participants each will be invited to participate and allocated to intervention or control conditions. The final target sample will comprise 360 adolescents (120 adolescents per city; 180 adolescents in the intervention and 180 in the control group).

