### 2.3. Procedure

#### 2.3.1. School Recruitment and Randomization

A list of all public high schools from each of the participating cities will be obtained from the educational government institutions (see Figure 3). The schools will be randomly selected in each city separately and a final ordered list will be created. The inclusion criteria for schools´ participation will be: (1) the school must have at least 2 class groups of 3rd grade of secondary education, (2) each class group must include at least 15 adolescents, (3) there must be at least 15 informed consents per class group, (4) the adolescents must have not taken part in other interventions to promote ACS or PA during the PACO study intervention period, and (5) the school must not offer bus transportation to the adolescents. If a school decides not to participate in the study, the same procedure will be carried out with the next selected school from the ordered list.

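### The arm appears to be attached to schools at the random draw, before invitation, replacement of refusers, teachers' choice of classes and consent, and none of these steps is protected from knowledge of the arm

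*Protocol article*

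**What the plan says.** The relevant statements are spread over several sections of the protocol article.

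- **Draw and arm (2.1 Study Design):** "Six high schools (i.e., an intervention and a control school in each of the 3 involved cities) will be randomly selected to participate". Schools are the unit of randomisation.
- **Draw and arm (2.2 Study Population):** "Within each city, 2 high schools, randomly selected and allocated to intervention or control treatment, will participate in the study". The sentence that follows, on classes, mentions invitation first and allocation second.
- **Ratio (2.3.3):** allocation is 1:1 within city. No timing is given.
- **Invitation (7. Discussion):** all schools in the three cities are "included in the random selection processes and then, the chosen schools will be invited to participate".
- **Refusal (2.3.1):** "If a school decides not to participate in the study, the same procedure will be carried out with the next selected school" on the ordered list.
- **Classes (7. Discussion):** "the school teachers will be able to choose the participating class groups, within the same grade". The reason given is that this raises teachers' involvement in the intervention.
- **Pupils (2.3.2):** staff recruit by visiting the classes already selected, and signed parental consent is required.
- **Eligibility that depends on consent (2.3.1):** "there must be at least 15 informed consents per class group".
- **Analysis (6. Data Analysis):** the primary analysis is by intention-to-treat on the groups originally assigned. Baseline comparisons and a long covariate list are also planned.

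**The concern.** Randomisation protects only what is fixed when the arm is assigned. If the arm goes with the draw and is known afterwards, four later decisions can depend on it: whether the school agrees, which classes the teacher offers, which families consent, and whether the school reaches the consent threshold or is replaced.

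The two arms ask for different things. The intervention takes 60 + 120 + 120 + 120 = 420 min (7 h) of physical education time, needs bicycles and helmets, and includes riding in traffic. The control arm continues as usual apart from the assessments. Section 3.2 accepts that not every pupil can be expected to bring a bicycle. A teacher who knows the school is in the intervention arm therefore has a practical reason to offer a class that is well equipped or keen, and a control teacher does not.

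At stake is whether a difference in cycling to school, active commuting or physical activity reflects the intervention or the readiness of those who came in. The article names the randomised design as a main strength, and its stated limitations do not mention selection after the draw.

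**Working it through.** The point depends on the order of steps. There is no stated figure to reproduce.

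**1. The order in the text**

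| Step | Where | What it implies about the arm |
|---|---|---|
| Random draw of schools | 2.1 | Arm named as part of the draw |
| Selection and allocation | 2.2, sentence on schools | Named together, before participation |
| Classes | 2.2, sentence on classes | Invitation mentioned before allocation |
| Invitation of schools | 7 | After the random selection; allocation not mentioned |
| Replacement of refusers | 2.3.1 | After invitation; no limit such as only before allocation |
| Choice of classes | 7 | By teachers; not stated to be blind to arm |
| Recruitment and consent | 2.3.2 | After the classes are selected |
| Consent threshold | 2.3.1 | Can be checked only after consent, yet decides school eligibility |

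The first two rows put the arm at the draw. The third can be read the other way. The remaining rows come after the draw, and no shown text keeps schools, teachers, families or recruiters unaware of the arm at those steps.

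**2. What the planned analysis can repair**

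Refusing schools, unchosen classes and families who decline never enter the analysis set, so intention-to-treat cannot restore them. Covariates such as bicycle ownership and school engagement, and a change-from-baseline analysis, can remove measured differences. They cannot remove unmeasured readiness to start cycling.

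**3. Scale, from the article's own figures**

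- Three schools per arm: one replaced school is 1/3 of an arm.
- Classes of about 30 with a threshold of 15: a class can qualify with 15/30 = 50% consenting.
- The introduction puts cycling to school below 2%. With 180 per arm that is fewer than 0.02 × 180 = 3.6 pupils, so a few receptive pupils could move this outcome.

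**4. Illustration under assumptions**

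The article gives no intraclass correlation (ICC) and no number of classes per school, so the values here are assumed. Suppose intervention teachers pick the best 2 of k classes, control teachers pick at random, and class effects are normal with variance equal to the ICC (total SD = 1). The expected gap between arms is c(k) × √ICC. Simulation gave these gaps:

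| ICC | k = 2 | k = 3 | k = 4 | k = 5 |
|---|---|---|---|---|
| 0.02 | 0 | 0.060 | 0.094 | 0.117 |
| 0.05 | 0 | 0.095 | 0.149 | 0.185 |
| 0.10 | 0 | 0.134 | 0.210 | 0.262 |

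For a gap of b SD with no true effect, the chance that a two-sided 5% test rejects is 1 − Φ(1.96 − b/SE) + Φ(−1.96 − b/SE), with SE = √(2/n). Pupils are treated as independent so that only the effect of the gap shows.

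- n = 180 per arm, SE = √(2/180) = 0.105: about 16% at b = 0.1 and 48% at b = 0.2.
- n = 150 per arm, SE = √(2/150) = 0.115: about 14% and 41%.

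This is deliberate selection in one arm only, with no baseline adjustment. It shows that a modest gap matters; it does not estimate the bias in this trial.

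**The case against.** A reader might infer that schools are definitely put into an arm before they agree, and that the randomisation is therefore broken. The documents do not support that. Sections 2.3.1 and 7 place random selection, not allocation, before invitation. Section 2.1 may simply describe the end result of one school per arm in each city. Section 2.2 can be read either way. Figures 2 and 3, which may show the sequence, are not reproduced in the text available for review. This stands, and it is why the conclusion is conditional.

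A reader might also infer that teacher choice is a bias in itself and affects every class. That is too strong as well. The choice is open to teachers in both arms. If made blind to arm, it does not bias the comparison. A school with exactly two third-grade classes is eligible and leaves nothing to choose. The stated motive of greater involvement does not prove that teachers know their arm when choosing.

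Other mitigations are real but partial:

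- Both arms carry a substantial assessment burden: 3 sessions × 1 h × 2 time points = 6 h, plus accelerometry, GPS and questionnaires. The contrast in demand is smaller than 7 h against nothing.
- Bicycle lending and sharing are planned.
- The article openly presents teacher choice and draw-then-invite as pragmatic adaptations, and lists uncertain teacher engagement as a limitation.
- The Reach component reports how many pupils are recruited.

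None of these keeps the arm out of refusal, class choice and consent. Concealment detail might be left to a fuller protocol. However, the article does set out these steps, and the sequence it gives leaves them open to knowledge of the arm.

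**Conclusion.** The point holds in conditional form. As written, the protocol appears to attach the arm to the draw and does not protect replacement, class choice, recruitment, consent or the consent threshold from knowledge of it. Because section 2.2 can also be read as invitation before allocation, sections 2.1 to 2.3.2 and section 7 must be reconciled. If the arm is known at those steps, selection can differ by arm, and with three schools per arm it cannot be relied on to average out. Intention-to-treat and baseline adjustment would not fully repair it.

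The size cannot be computed from the documents. The gaps of 0.06 to 0.26 SD in the illustration rest on an assumed ICC of 0.02 to 0.10, three to five classes per school and deliberate one-sided selection. With two classes, or with choice blind to arm, the contribution from class choice is zero. The change is worth making because it is cheap, but actual bias is not established.

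**What to change.** Keep the random ordered list and the teachers' choice, and fix the sequence in sections 2.1 to 2.3.2 and 7. In each city:

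1. Go down the ordered list until two schools agree in writing to accept either arm. Replace refusing or ineligible schools only at this stage, before allocation.
2. Have the teachers name the two classes in each school.
3. Obtain parental consent, check the consent threshold and complete baseline.
4. Then randomise the two schools 1:1, by someone not involved in recruitment. After this, a school is not replaced and stays in its arm for the analysis.
5. Report refusals, replacements and reasons, the number of third-grade classes available and chosen, and consent rates by school.

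If baseline before allocation is not feasible, at least keep schools, teachers and recruiters unaware of the arm until class choice and consent are complete.

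The cost is wording and sequence. Sample size, outcomes and session content do not change. Schools learn their arm later, so the intervention schools have less time to arrange bicycles, instructors and timetables, and the two schools in a city must be ready together. Provisional session dates in both schools would ease this.

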## 8. Conclusions

The PACO study will implement a school-based intervention to promote cycling. It will yield a comprehensive understanding of the effects of the intervention on cycling to school behaviour, ACS, PA, basic psychological needs satisfaction in ACS, motivation for ACS, adolescent´s and parental perceived barriers to ACS and peer social support for ACS in Spanish adolescents. Moreover, the PACO study will examine the mediator effect of the previous variables in the adolescent´s cycling and ACS behaviours and overall PA. This intervention will contribute to promote a healthy active commuting behaviour among adolescents to create more liveable and sustainable cities. The PACO study findings have potential to provide guidance for teachers, researchers, and policy makers to implement effective interventions to promote cycling to school and contribute to healthier societies.

## Figures and Tables

**Figure 1 ijerph-18-02066-f001:**
[figure not shown]
The “Pedalea y Anda al COle” (PACO) study logic model. Note: RCT: randomized controlled trial; ACS: active commuting to and from school; PA: physical activity; SDT: self-determination theory; SEM: social-ecological model; RE-AIM: reach, effectiveness, adoption, implementation, maintenance.

**Figure 2 ijerph-18-02066-f002:**
[figure not shown]
Cities, schools, and adolescent participants in the PACO study.

**Figure 3 ijerph-18-02066-f003:**
[figure not shown]
Plan flow chart of the PACO study.

**Figure 4 ijerph-18-02066-f004:**
[figure not shown]
Structure and duration of the school-based intervention to promote cycling to school.

**Figure 5 ijerph-18-02066-f005:**
[figure not shown]
The measurement procedure of the PACO study.

**Table 1 ijerph-18-02066-t001:** Summary of the variables and instruments, following the levels of influence of the social-ecological model (SEM).

General Variable	Specific Variables	Instrument
**Individual**		
Sociodemographic characteristics	Age, school grade and class, gender, full postal address, bicycle ownership	Student questionnaire
Behaviour	Cycling and active commuting to/from school (ACS) Physical activity (PA) Cycling knowledge, cycling skills	Mode and Frequency of Commuting to/from School questionnaire [60,61] Family commuting-to-school behaviour questionnaire [62] Accelerometer Youth Activity Profile questionnaire [63] Cycling Tests
Perceptions	Perceived barriers to active commute to school	Barreras en el Transporte Activo al Centro Educativo (BATACE) questionnaire [64]
Psychosocial	Autonomy, competence, and relatedness satisfaction in ACS Motivation for ACS	Basic Psychological Need Satisfaction in Active Commuting to and from School questionnaire [65] Behavioural Regulation in Active Commuting to and from School questionnaire [66]
Anthropometric	Weight, height, waist circumference, body mass index	Weighting platform Seca 876 Height meter Seca 2013 Non-elastic tape measure Lufkin W606pm
**Interpersonal**		
Parental sociodemographic data	School name, age, gender, children´s gender, and full postal address	Family questionnaire
Family socioeconomic status	Family income Parental educational level	Family Affluence Scale (FAS) questionnaire [67] Family questionnaire
Parental perceptions	Barriers to allow their children to ACS	Parental Perception of Barriers towards Active Commuting to School (PABACS) questionnaire [68]
Peer social support	Peer social support	Family questionnaire
**Community**		
School Characteristics	Student enrolment, socioeconomic status and school engagement	Electronic and manual Search, Geographical Information System,
City Characteristics	Population density and city income	Tax Agency, Spanish Public Ministry of Finance and Public Administration of Spain
**Environment**		
Distance home-school	Shortest route, real route	Google Maps Global Positioning System (GPS)
School Neighbourhood	Cycling lane length Bicycle racks	Geographical Information System Manual Search
Weather	Temperature (maximum, minimum, mean), total rainfall, and mean wind speed	National Weather Data Bank

**Table 2 ijerph-18-02066-t002:** Reach Effectiveness Adoption Implementation Maintenance (RE-AIM) components and dimensions to be evaluated in the PACO study.

RE-AIM Component	PACO Study
REACH (R)	The absolute number and proportion of participants recruited for the study given a target sample of 360 adolescents aged 14–15 years old from the 3rd grade of secondary education.
EFFECTIVENESS (E)	Main outcomes: cycling to school, ACS—walking and cycling, and PA Other variables: cycling knowledge, cycling skills, basic psychological needs satisfaction in ACS, motivation for ACS, barriers to ACS from adolescents and parents, and peer social support for ACS.
ADOPTION (A)	The absolute number and proportion of school staff who are willing to deliver the intervention. Alignment/consistency between intervention content and national educational policy [55].
IMPLEMENTATION (I)	Intervention fidelity: extent to which intervention agents deliver the intervention components as intended, including adaptations made, and of participant compliance with the intervention in terms of attendance. Cost of the intervention Process evaluation: participant feedback about enjoyment, usefulness, and potential improvements after each session. Participant focus groups and interviews with intervention agents at the end of the intervention to understand their experiences of the intervention.
MAINTENANCE (M)	Setting level: extent to which the intervention is delivered as part of the school PE curricula the following academic year. Individual level: follow-up questions to the PE teachers after 6 months post-intervention to assess the intervention´s maintenance.

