## 5. The RE-AIM Framework

The RE-AIM framework provides key indicators for assessing the internal and external validity of the PACO study, which are shown below (see Table 2).

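### Reach is measured against the planned sample of 360, so it shifts with class size, cannot register school refusals, and is weak support for external validity

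*Protocol article*

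**What the plan says.** Section 5 of the protocol article introduces the RE-AIM indicators of Table 2 as "key indicators for assessing the internal and external validity of the PACO study". The Reach row of that table reads "The absolute number and proportion of participants recruited for the study given a target sample of 360 adolescents". The Adoption row begins with "The absolute number and proportion of school staff who are willing to deliver the intervention"; its other item is agreement with national educational policy.

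Section 2.2 explains where 360 comes from: two schools in each of three cities, with two class groups of about 30 invited in each school. Section 2.3.1 adds two rules that affect the count:

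- When a school declines, "the same procedure will be carried out with the next selected school from the ordered list". No limit on replacements is stated.
- For a school to qualify, "each class group must include at least 15 adolescents" and "there must be at least 15 informed consents per class group".

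Section 2.3.2 requires signed parental consent from each pupil. It describes no replacement of pupils who do not consent.

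**The concern.** Reach is meant to show what share of the people offered a programme took part. Here the denominator is a planning figure fixed before any school is approached. It contains neither the number of pupils actually in the invited classes nor the schools that said no. Three consequences follow:

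- two trials with the same participation can report different Reach if their classes differ in size;
- the consent rule removes low-consent schools from the ratio instead of counting them;
- school refusal, which Section 2.3.1 plans for and which Section 7 makes plausible by noting that earlier emails to schools went unanswered, leaves no trace.

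At stake is the reading of external validity. The limitations and strengths in Section 7 list the RE-AIM validity indicators among the strengths of the study. A reader who takes recruited/360 for participation could be misled in either direction.

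**Working it through.** **Inputs from the article.** Six schools and two classes per school of about 30 pupils (Section 2.2); at least 15 pupils and at least 15 consents per class (Section 2.3.1); denominator 360 (Table 2).

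**Assumptions.** The article gives no refusal or consent rates. Class sizes other than 30, consent rates and numbers of schools approached below are illustrations.

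**1. Reproduce the stated figure.** 6 x 2 x 30 = 360. The target equals the approximate number of pupils invited.

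**2. Formula.** With class size m and pupil consent proportion c, the Table 2 indicator is (6 x 2 x m x c) / 360. Participation in the invited classes is c. The two agree only when m = 30.

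**3. Classes of 30.** Consent of 50%, 75% and 100% gives 180, 270 and 360 recruits, so the indicator reads 50%, 75% and 100%. Here it works as a measure of pupil consent.

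**4. Other class sizes.**

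| Class size | Consent | Recruited | Recruited/360 |
|---|---|---|---|
| 20 | 100% | 240 | 67% |
| 25 | 100% | 300 | 83% |
| 35 | 60% | 252 | 70% |
| 35 | 100% | 420 | 117% |

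Full participation in classes of 20 scores lower than 60% participation in classes of 35, and the proportion can exceed 100%.

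**5. Floor.** With six schools enrolled, the consent rule gives at least 6 x 2 x 15 = 180 recruits, and 180/360 = 50%. That reading of 50% fits consent of 50% in classes of 30, 60% in classes of 25, 75% in classes of 20, or 100% in classes of 15. In each case 15 pupils per class consent.

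**6. School refusals.** Take classes of 30 and 75% consent, so that 6 x 2 x 30 x 0.75 = 270 pupils are recruited. Compare recruited/360 with recruited pupils over pupils in two classes of every school approached (60 per school).

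| Schools approached | Recruited/360 | Recruited / pupils in approached schools |
|---|---|---|
| 6 | 75% | 270/360 = 75% |
| 8 | 75% | 270/480 = 56% |
| 12 | 75% | 270/720 = 38% |
| 24 | 75% | 270/1440 = 19% |

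The Table 2 indicator is constant in the number of schools approached.

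**The case against.** The best defence is that 360 is also about the number of pupils invited, so with classes near the planned 30 the ratio is a fair estimate of pupil participation. That stands, and it rules out a stronger reading that a reader might infer: that replacing refusing schools drives Reach towards 100% whatever the true participation. Only schools are replaced. With classes of 30, consent between 50% and 90% gives 180 to 324 recruits and a reading of 50% to 90%. For the same reason it would be wrong to say that no indicator reflects pupil refusal.

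A second defence is that school uptake belongs under Adoption, that a proportion of willing staff implies a denominator including unwilling staff, and that counts of approached schools may sit in the flow chart (Figure 3), which could not be seen here. It is fair that missing counts in a condensed article are no fault, and the fix below does place school uptake under Adoption. But Table 2 does not say which schools supply the staff. Section 3.2 has an expert cycling teacher lead all sessions while physical education teachers attend and support, so staff willingness is not the same thing as school uptake. A flow chart would also leave the stated definition of Reach unchanged.

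Third, Reach is descriptive. It enters no effect estimate or test in Section 6, Section 3.2 makes scale-up conditional on effectiveness, and the absolute number recruited is reported as well. All of this stands and limits the severity.

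**Conclusion.** The point holds as a poorly chosen denominator that the article itself states, not as missing detail. Recruited/360 approximates pupil consent when classes hold about 30. Otherwise it mixes consent with class size: 67% at full consent in classes of 20, 70% at 60% consent in classes of 35, and 117% at full consent in classes of 35. With all six schools enrolled, each with two qualifying classes, it has a floor of 50%. It cannot register school refusals, and the Adoption row does not state a measure that would.

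It would go too far to conclude that Reach says nothing about external validity, since it carries some information on participation within the enrolled schools. It is weak support for that purpose. The floor, the reproduction of 360 and the insensitivity to school refusals follow from the stated rules. The percentages by class size and number of schools approached rest on the illustrative inputs shown. Severity is low because no effectiveness result depends on this indicator.

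**What to change.** - **Reach:** define it as consented eligible pupils divided by all eligible pupils enrolled in the invited classes. Count eligibility before consent, because Section 2.3.2 makes signed parental consent itself a condition of eligibility, and a denominator restricted to consenters would give 100% by construction.
- **Adoption:** add schools accepting divided by schools approached on the ordered list, by city. Keep in the denominator the schools excluded for too few consents.
- **Recruited/360:** keep it, labelled as recruitment progress.

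The consent forms and the ordered list are already part of the procedure in Sections 2.3.1 and 2.3.2, and class rosters should be obtainable from the schools. The cost is a little extra counting and possibly a less favourable figure. Sample size, outcomes and effectiveness analyses are unaffected.
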